**2.3 Procedures of recruitment, registration, and randomization**

**2.3.1 Recruitment**:

Patients prescribed 9INH therapy will be asked, by their TB care provider, for permission to be contacted by study personnel. Those that agree will be approached to verify eligibility, and obtain signed informed consent. (See Research module Appendix 1 – informed consent used in Phase 2)

**2.3.2 Registration**

Once subjects have provided informed consent, research staff will access the registration and randomization website via the Internet. This computer based program will be available 24 hours/day and 365 days/year.

**2.3.4 Rationale for stratification by centre**

The characteristics of the patient populations, their risk of TB, as well as physicians’ usual practice – in starting LTBI therapy, or stopping it because of patient intolerance, will vary considerably by centre. Randomization stratified by site should ensure that these and other potential sources of bias by centre are balanced. As well this will ensure that balance is maintained if one or more centres stop enrolling 166, as occurred in Phase 2.

**2.3.5 Maintaining Confidentiality**

The Web-based registration system is non-nominal. At the time of registration, all patients are assigned a unique study ID number. This will be used to label forms, clinical data, and all case report forms. All patient information sent to the data coordinating centre, or reviewed by independent panels, will contain only the study ID. All contact information including names, address, telephone numbers, other contact persons, and full date of birth will be stored at each site, in a secure location, and safeguarded by the site PI. In Canada, lists of participants’ names will be forwarded by registered courier to Provincial health authorities to assess if they develop active TB, following procedures approved by provincial privacy commissions. At the international sites the patients’ names will be cross-checked against reported TB cases at State, or National level, using appropriate safeguards for patient confidentiality. Protocols will be written for protection of confidentiality; these will be a focus of training and ongoing monitoring of all sites.

**2.4 Protection against bias**

**2.4.1 Preventing bias in ascertainment of the primary outcome of active TB**

Given the absence of blinding, it is important to control for potential bias in ascertaining the primary study outcome. To reduce bias in finding or diagnosing cases, the questionnaire used for follow-up, and the clinical evaluation including diagnostic procedures for active TB will be standardized. The diagnostic process may vary if subjects seek care from non-study providers, but this should not be biased by the LTBI regimen. Each member of the clinical panel will review all available clinical evidence including X-rays, pathology, and microbiology reports, while blinded to subjects’ identities, LTBI therapy, and opinions of the other panel members. Each will independently determine if the definition of confirmed active TB is met – ie positive cultures or nucleic acid amplification test for *M. Tuberculosis*, or positive biopsy (see Section 2.8.1 for details). These objective microbiological criteria should not be influenced by patient, nor provider bias, and are the standard outcome for all LTBI trials 33, 61, 65, 68, 104, 128.

**2.4.2 Preventing bias in ascertaining secondary outcomes**

The secondary outcome of probable TB, defined as compatible clinical and radiographic features will be judged by the same 3-member clinical review panel, using the same approach as above. All possible Grade 3 or 4 SAE will be investigated using standardized protocols, and graded according to ATS guidelines for hepato-toxicity 155, or the National Cancer Institute Common Terminology Criteria for Adverse Events v2.0 (at <http://ctep.info.nih.gov/reporting/ctc.html>) for all others. Grading, and attribution of cause, will be performed by three independent reviewers blinded to the identity of patients, study drug, and opinions of the other reviewers. We will ascertain costs based on visits, tests and other health services – all of which are quite objective. To further minimize bias, the laboratory technicians who perform cultures and drug sensitivity testing, and the cost-effectiveness analyst will be blinded to study regimen.

**2.5 Inclusion and exclusion criteria**

**2.5.1 Inclusion criteria**

Adults (age > 18) with documented positive TST as defined below and prescribed 9INH for LTBI, following authoritative recommendations 107, 138:

**Note:** In the absence of a TST test, a positive QFT (or T-Spot) (according to manufacturers recommendations) (see screening, recruitment and randomisation procedures) is equivalent to a TST of 10 mm.

1. HIV positive , OR to start TNFa inhibitors, OR on transplant anti-rejection medications.(TST ≥5 mm or QFT +)

1. Close contact: >4 hours contact per week, for > 1 week with person with active pulmonary TB. (TST >5 mm or QFT +)
2. Apical/upper lobe fibronodular disease with area >2cm2 (shown in RCT Quick Guide) (TST >5 mmor QFT +)
3. Documented tuberculin conversion within two years. (Increase ≥ 6 mm, with subsequent TST >10 mm or QFT +)
4. Diabetes, renal failure, or immuno-compromised from medical condition or therapy (TST >10 mm or QFT +)
5. Casual contact: contact of <4 hours/week, with a person with smear positive pulmonary TB. (TST >10 mm or QFT +)
6. Tuberculin conversion within 2-5 years. (Increase of 10 mm or more with subsequent TST >10 mm or QFT +)
7. Have (1) **TWO** of the following  **four** factors if TST = 10-14mm or QFT +,

**OR** (2) **ONE** factor if TST >15mm:

- 1. Arrival in Canada, Australia, or Saudi Arabia in the past 2 years from countries with WHO estimated incidence greater than 100 per 100,000 (these are listed in the RCT Procedure guide - Appendix 5)
  2. BMI <19 (BMI calculations, see RCT Procedure guide);
  3. Any abnormality on chest x-ray compatible with past-TB infection e.g. calcified granuloma, or hilar lymph nodes, costo-phrenic angle blunting - other than fibronodular disease above.
  4. Cigarette smoking (at least a half pack per day) currently.

In the low and middle-income countries, LTBI therapy will usually be offered only to patients in categories 1& 2158, because of resource limitations, resulting in substantial differences in risk of active TB among untreated patients at the different sites. Balanced allocation of risk groups to the two study arms will be maintained by site-stratified randomization.

**2.5.2 Exclusion criteria**

1. Patients who were contacts of TB cases known to be resistant to INH, RIF, or both (i.e. MDR)107, 138,127.

2. Known HIV-infected individuals on anti-retroviral agents whose efficacy would be substantially reduced by Rifampin, unless therapy can safely be changed to agents not affected by Rifampin (listed in RCT quick guide - Appendix 5).

3. Pregnant women - Rifampin and INH are considered safe in pregnancy 138, 167, but therapy is usually deferred until 2-3 months post-partum to avoid fetal risk and the potential for increased hepato-toxicity immediately post partum 168.

4. Patient on any medication with clinically important drug interactions with INH or RIF, which their physician believes would make either arm contra-indicated. An updated list of clinically important drug interactions is in the RCT Quick Guide (Appendix 5). This includes women taking hormonal contraceptives who will not take alternative contraception.

5. History of allergy/hypersensitivity to Isoniazid or to Rifampin, Rifabutin or Rifapentine.

6. Active TB. Patients initially suspected to have active TB can be randomized once this has been excluded.

7. Persons who have already started LTBI therapy.

**2.5.3 Rationale for exclusion criteria**

We are interested in the real world application of Rifampin, and so will include persons potentially at risk for non-completion or for adverse events. To obtain a realistic estimate of safety and tolerability, no patient will be excluded on the basis of age nor history of TB therapy, liver disease, alcohol use, or other medication use (except as specified above). If the treating physician prescribed LTBI therapy, they must have concluded the benefits of therapy outweighed the risks. Similarly, to obtain a realistic estimate of effectiveness, patients at risk of non-completion (homeless, alcoholic, and drug use) will be included. An additional reason for these inclusion criteria is to enhance comparability with earlier trials 169 - which involved subjects who were older33, 65, 161, HIV infected68, 104, or had other co-morbidities62.

**2.6 Duration of treatment**: (see section 2.2 – Interventions)

**2.7 Follow-up and data gathering**

**2.7.1 Initial evaluation**

The initial evaluation, completed by study personnel, will include demographic information, past medical history, reasons for LTBI therapy, tuberculin reactions, chest X-ray findings, other investigations, and HIV status if known. In contrast to patients with active TB, HIV testing of LTBI candidates is not considered essential for patient care 107, 138, 158. Hence HIV testing will be offered to all subjects, with appropriate counselling, although it will not be a required test for inclusion in the study. The need for other investigations is at the discretion of the provider, except for subjects with chest X-ray abnormalities with lesions > 2cm2, or close contacts with symptoms or X-ray abnormalities, in whom sputum specimens must be sent for AFB smear and culture 107, 138. If investigations to exclude active TB are performed, patients can not be enrolled until results are available. We have developed a draft algorithm to identify and investigate subjects with possible active TB (RCT Appendix 3). This will be evaluated and validated to facilitate the use of LTBI therapy in resource-limited settings after the trial is completed.

**2.7.2 Follow-up during treatment**

We wish to ascertain treatment effectiveness under routine programme conditions. Therefore, follow up will be in line with standard practice, and conducted by the initial treating physicians and TB clinic staff, meaning that visits will be monthly for the first 2 months, then every 2 months (minimum) thereafter for both treatment regimens. Blood count (CBC), and liver transaminases will be checked pre-treatment and at the first follow-up visit. Patients will be encouraged to call, or see their TB therapy provider or TB clinic staff, if they develop any new symptoms. Concomitant treatment is a potential problem with un-blinded therapy 166 but given the specificity of anti-TB drugs it is highly unlikely that any such therapy would be given, unless active TB was diagnosed. To monitor drug interaction, for medications whose drug levels can be monitored, these will be measured at 0, 2, 4 and 8 weeks, along with any related dosage changes. For anti-coagulants, anti-diabetics, anti-hypertensives or lipid lowering agents the clinical end-points will be monitored - at 0, 2, 4 and 8 weeks of therapy, plus related dosage changes.

**2.7.3 Post treatment follow-up**

After treatment is finished (or discontinued) post-treatment follow-up by telephone, or visit – at the subject’s home, or at the health facility will begin. Follow-up will be every 3 months until 28 months post randomization on the date corresponding to 3 monthly intervals after randomization. Follow-up frequency is because of experience gained with Phase 2 participants – frequent contacts are needed, even if brief, to enhance retention, because so many move, change telephones, or lose interest. Our objective is to achieve a drop-out rate less than 10%.

**2.7.4 Maintaining high quality data:**

*2.7.4.1 Training:* At the start, we will hold a two day training course for all investigators and research coordinators (see Appendix 7- Time-Table) to review eligibility criteria, ethics, consent procedures, protection of confidentiality, registration, randomization, reporting of serious adverse events, and follow-up procedures during and after treatment. Particular attention will be paid to procedures to minimize drop-outs, investigation and management of SAE during therapy, and ascertainment of active TB. Staff at new sites will receive additional intensive training at the study coordinating centre

*2.7.4.2 Supervision:* The PI will visit all new sites within three months after beginning randomization, and all sites annually. The study coordinator will visit new sites at the time of trial initiation, all sites every three months in year 1 and every six months thereafter. We will verify that patients are approached, informed, and provide consent correctly. We will ascertain that documentation of IRB correspondence and consents are complete, confidentiality is protected, and that data entered in databases, or using the Web-based programmes, corresponds to source documents. Verbal feedback will be provided to staff immediately, and written reports will be reviewed with the site investigators and staff, and the principal investigator.

*2.7.4.3 External Audit:* For all Canadian sites, we plan two independent audits – the first 6-9 months after starting enrolment, and the second 18 months later. Both will be performed by a professional clinical research associate experienced in auditing pharmaceutical sponsored trials. For budgetary reasons, the professional auditor will make only one visit to each international site - one year after beginning randomization. The PI will make the second audit visit 12 months later.

*2.7.4.4 Electronic databases - web based and local***:** The web based initial registration incorporates all information from the initial case report form. All SAE and active TB will also be reported using non-nominal web-based forms. To collect all other treatment phase, and post-treatment follow-up information, site staff will use local databases. The data will then be transferred –in non-nominal form- to the coordinating centre. All web-based forms and randomization software, as well as local databases were developed in Phase 2, except for reporting the primary outcome of active TB - which will be added.

**2.8 The primary and secondary outcomes:**

**2.8.1 Definition of the primary outcome**

Confirmed active TB during 28 months after randomization will be defined as a positive culture for *M. tuberculosis*, positive Nucleic acid amplification test for M TB complex, or caseating granulomas in a biopsy from any site. Positive AFB smears will be considered false positive if cultures are negative, but will be considered confirmatory, if cultures failed (for example if contamination or other technical problem occurs).

**2.8.2 Definition of the secondary outcome of probable active TB**

Probable active TB during 28 months after randomization will be defined as a compatible abnormal chest X-ray plus clinical symptoms, which improve following treatment for active TB, as judged on blinded review by a majority of the independent clinical review panel members.

**2.8.3 Other secondary outcomes**

See below for compliance, serious adverse events, costs, and drug resistance.

*2.9.1.3 Assessing completeness of ascertainment of active TB****:*** To verify the completeness of ascertainment of active TB with our proposed method of follow-up, we will send a list of all randomized subjects to public health officials responsible for the TB registry in each jurisdiction. They will match subjects names with nominal registries held at provincial, state, or national levels. This is included in the consents for Phases 2, and 3 (Research Module Appendix 1). This will allow us to ascertain any under-estimate of the primary outcome, although patients with clinically diagnosed TB, and those who developed TB after leaving the province/state where enrolled may be missed. We will use the same verification procedure for the international sites. In Canada, provincial registries are almost 100% complete for microbiologically confirmed cases, but the completeness, accuracy and comparability of the TB registries at the international sites are unknown. However any possible differences in detection between sites should not bias the comparison of regimens, given the stratified randomization by site.

For the Canadian sites we will ascertain outcomes of consenting participants who were lost to follow-up, through the provincial health administrative databases. We will forward the names of these subjects, to the provincial health authorities 28 months after randomization, to verify whether they have died (if so, date of death), or moved out of province (if so, when). This will enable us to ascertain outcomes of such subjects, and to examine potential bias due to these drop-outs.

**2.9.2 The secondary outcome of compliance during treatment**

Compliance with treatment is an important modifier of treatment effect, and must be measured to perform the planned efficacy analysis among the sub-groups who take therapy per protocol. In Phases 1 & 2 we used the Medication Event Monitoring System (MEMS), to record pill taking behaviour. However we plan to use pill counts as our primary method of assessing compliance because: (i) pill counting is inexpensive, and feasible for all programmes – hence results can be more easily reproduced elsewhere; (ii) in Phase 2 pill counts were highly concordant with the MEMS records (iii) the MEMS is very expensive, and so is unlikely to be adopted in practice – even in North America; (iv) in a previous trial, pill counting had excellent predictive value for risk reduction 65.

**2.9.3 The secondary outcome of serious adverse events (SAE)**

At each follow up visit patients will be questioned and examined for evidence of adverse events. Prior to beginning therapy and at the first follow-up visit, CBC, and liver transaminases (AST and ALT) will be tested. As in Phase 2, (see Section 2.19) site investigators will file an initial web-based SAE report if therapy is discontinued because of patients’ symptoms or lab abnormalities. They will be investigated and managed following standardized protocols developed in Phase 2 (RCT Appendix 2), based on our published experience 170, recent reviews 154, 155 and authoritative guidelines 138, 155. Adverse events will be graded as suggested in guidelines by the American Thoracic Society for hepato-toxicity 155, and the National Cancer Institute Common Terminology Criteria for Adverse Events v2.0 (at <http://ctep.info.nih.gov/reporting/ctc.html>;). As in Phase 2 we will have an independent 3 member panel ([name] [name], [name], and [name] - letters in Research Module Appendix 1). This panel will review all possible SAE – defined as events that lead to permanent physician discontinuation of study drug, without knowledge of study drug, nor opinions of neither other panel members nor treating physician. They will judge type, severity, and probability of cause of the SAE. Differences will be resolved by consensus. Results of this blinded review by the independent panel will be considered the final diagnosis for type, severity, and relationship to the study drugs. Detection of Grade 3-4 reactions may be greater than in routine practice, but this should occur equally for both arms, and enhance research subjects’ protection. Unreported adverse events cannot be reviewed - leaving room for provider bias. This may occur with minor intolerance, (which will be termed patient non-compliance). However, if the provider stops therapy because of adverse events, this must be reported by investigators, and investigated as above.The anticipated number of participants in each arm will provide substantial power to detect relatively small differences in occurrence of SAE. This should provide the opportunity to detect less common SAE, such as hematologic complications, or ascertain if differences occur within subgroups (e.g. HIV infected). (See also Section 2.18).

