**1.6 Risks for the trial participants**

Available evidence, from *millions* of patients treated for active TB with RIF in combination with other drugs 154, 155, suggests that RIF is well tolerated and safe. Hepatitis is the most important and potentially fatal complication of INH and RIF-PZA therapy of LTBI. On the other hand, mono-therapy with RIF has been associated with very low rates of hepatitis – in Phase 1&2 131, 148, and elsewhere 33, 121-124 (RCT Appendix 1 - Table 5). Nevertheless, in view of the 2RIF-PZA experience, where initial trials suggested excellent safety, but unacceptable toxicity was seen with introduction into routine practice, it is prudent to continue to closely monitor the safety of 4RIF. This will be done by independent review of all possible Grade 3 or 4 SAE, plus periodic interim analyses of safety during the trial. Patients will be carefully questioned regarding concomitant medications, to identify potential drug interactions, and will be excluded if these can not be managed easily. Mono-therapy of patients with unrecognized active TB, of particular concern in HIV infected patients, may lead to drug resistance, which has serious implications for treatment152, 153. In all settings we will ensure that study participants have access to all necessary investigations to exclude active TB, including cultures. In some settings this means budgetary allocations to pay for these investigations if necessary. In the long term, 4RIF will not be useful in resource-limited settings if extensive investigations are needed before starting therapy. Hence, we will develop and evaluate low cost diagnostic algorithms to identify candidates for LTBI therapy likely to have active TB, for use after the trial (RCT Appendix 5). Initial or primary drug resistance can render LTBI therapy ineffective 127. However rates of RIF resistance rates are very low and much lower than INH resistance in all participating countries (RCT Appendix 1 - Table 6) 156, 157, enhancing the rationale and ethical acceptability of evaluating 4RIF. INH is recommended unless prevalence of primary drug resistance exceeds 50% 107, 158 - clearly not the case in any country, or if the subject is a contact of INH resistant cases INH 107, 138 – an exclusion criteria for this trial. Finally, subjects will be followed two full years after completing 4RIF to ensure early detection of active TB if this therapy fails.

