**SECTION 2 THE PROPOSED TRIAL**

**2.1 Study design**

We propose a multi-centre randomized 2-arm positive control open-label clinical trial. Patients prescribed standard therapy for LTBI (i.e. 9 months INH) will be approached to participate before they begin therapy. After providing informed consent, subjects will be registered using a web-based system, accessible at all times. This system will verify eligibility and perform immediate on-line randomization, using a computer generated random sequence, in equal numbers to 4RIF or 9INH - both daily and self administered. Randomization will be stratified by site and in blocks of variable length. The primary end-point will be the occurrence of microbiologically confirmed active TB. Secondary end-points include occurrence of confirmed and probable active TB, Grade 3 or 4 adverse events (SAE), drug resistant active TB, and health system costs. All primary outcomes will be reviewed by an independent 3-member clinical review panel, and all SAE will be reviewed by a different independent 3-member panel. Both panels will be blinded to the study drug, and patient identity.

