**2.18.3 SAE**

This outcome will be defined as the occurrence of Grade 3 or 4 SAE, diagnosed by the majority of the independent reviewers. Differences in all SAE, and by type of SAE between the two groups will be tested with Chi-squared or Fisher’s exact tests. Sub-group analyses will compare rates of SAE by age, sex and HIV status. Drug interactions with 4RIF are common, and of particular interest since this will be the largest trial with mono-Rifampin therapy. All analysis of SAE and drug interactions will be presented as exploratory, with appropriate caution 166, 196. However in view of the very limited published experience with 4RIF, any information about adverse effects, including drug interactions, would be very useful for clinicians.

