We experienced more difficulties recruiting patients than anticipated at several Canadian sites. In the first year we intensified training and supervision, and opened a new sub-site. When this was not enough, investigator and CIHR approval was sought to shift budget allocations from low enrolling sites to start two new international sites – in Brazil and Saudi Arabia, ***within the originally awarded total budget***. Enrolment at all sites subsequently increased to average 40 patients per month. We had planned a sample size of 549 per arm to provide 80% power (2 sided test) to demonstrate a significant difference in SAE rate if the true rate with 9INH was 4% and 4RIF was 9%, or was 5% with 9INH and 2% with 4RIF. After 25%, 50% and 75% of planned enrolment, the DSMB reviewed interim analyses – still blinded to the study drugs. In January 2007, the 3rd interim analysis revealed that SAE were significantly fewer in one arm. The DSMB asked to be unblinded, and when they learned that 4RIF had the lower rate of SAE, they recommended discontinuation of enrolment. Of 420 subjects randomized to 4RIF, 7 developed Grade 3-4 adverse events attributed to study therapy by the independent panel, compared to 17 of the 427 on 9INH (Risk difference (4RIF-9INH): -2.3%; [95% Confidence interval: -0.1% to -5%] p=.04). Grade 3-4 hepatitis occurred in 3 taking 4RIF, compared to 16 who started 9INH (-3.1%; [-1% to -5%], p=.003). Grade 1 or 2 adverse events attributed to study drugs were similar in the two arms. Asymptomatic reduction in platelet count and white blood count were significantly more frequent during treatment with 4RIF. Completion rates were 78% with 4RIF and 60% with 9INH (Risk difference: 18% [12% to 24%], p<.001) 148. Average health system costs were significantly lower with 4RIF. Incremental cost effectiveness analysis revealed that 4RIF would be cost saving and prevent more cases if efficacy was at least 75%, and would be cost saving if efficacy is more than 65% 147.

We believe that a study to assess effectiveness of 4RIF is now justified. This regimen has been demonstrated to have better completion, lower costs, and is safer than 9INH, particularly for hepatotoxicity - the most important and potentially lethal adverse event of INH therapy (and of 2RIF-PZA). In Phase 2, 847 subjects were enrolled, randomized, treated and followed to detect active TB - using the methods proposed here, making the present proposal more cost-effective.

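### Section 2.9.3 lets an unblinded decision to stop study drug select which Grade 3-4 events reach the blinded panel, so the safety comparison and its interim looks can be biased, in a direction the protocol does not reveal

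*Protocol*

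**What the plan says.** **What the outcome is meant to be.** Secondary objective (iii) in Protocol section 1.2 compares rates of Grade 3 and 4 adverse events during treatment between the randomized arms. Section 2.1 uses SAE for Grade 3 or 4 events. Section 1.6 promises "independent review of all possible Grade 3 or 4 SAE", and section 2.4.2 uses similarly broad wording. Section 2.18.3 says: "This outcome will be defined as the occurrence of Grade 3 or 4 SAE, diagnosed by the majority of the independent reviewers".

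**What reaches the panel.** In section 2.9.3 the panel reviews possible SAE, "defined as events that lead to permanent physician discontinuation of study drug". The site's own trigger is worded differently: "site investigators will file an initial web-based SAE report if therapy is discontinued" because of symptoms or laboratory abnormalities. That trigger is not expressly limited to permanent or physician-initiated stopping.

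**Who makes the decision.** Section 2.1 describes a "positive control open-label clinical trial", so the treating physician knows the regimen. Section 2.3.4 says that practice in stopping therapy for intolerance will differ considerably between centres.

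**What the protocol concedes.** Section 2.9.3 states: "Unreported adverse events cannot be reviewed - leaving room for provider bias". It then limits the scope: "This may occur with minor intolerance, (which will be termed patient non-compliance"). It also obliges investigators to report when the provider stops therapy for an adverse event.

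**Where the outcome is used.** Under section 2.17.2 the DSMB looks at SAE four months after 25%, 50% and 75% of subjects are randomized. It considers stopping if rates are significantly higher with 4RIF, at a nominal p of 0.018 per analysis.

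**The concern.** The objective and the analysis section describe an outcome defined by severity. The referral rule in section 2.9.3 defines it by severity and by what an unblinded physician did with the drug. If physicians are readier to stop one drug than the other for events of the same grade, the counts differ between arms even when the true Grade 3-4 rates do not.

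The protocol's concession does not cover this. It speaks of minor intolerance, whereas the gap concerns severe events after which the physician did not permanently stop the drug. Mandatory reporting of provider-stopped therapy applies only to events that have already met the condition. Stratification by site balances centres between arms. It does not remove decisions that depend on the regimen within a centre.

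Two things are at stake. One is the comparison that will carry the safety message of what the protocol calls the largest trial of rifampin alone for latent infection. The other is the DSMB's ability to detect an excess of severe events with 4RIF.

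**Working it through.** **1. Routes to the panel, reading section 2.9.3 as written.** Take a Grade 3-4 event during treatment and ask whether it has a stated route.

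| What happened to study drug | Site report triggered? | Meets the panel definition? |
|---|---|---|
| Permanently stopped by the physician | Yes | Yes |
| Temporarily held | Unclear | No |
| Stopped by the patient | Possibly, if because of symptoms | No |
| Continued | No | No |

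All four rows fall within objective (iii). Only the first has a stated route to review.

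**2. The stated interim level.** Simulating a constant two-sided boundary at nominal 0.018 with equally spaced looks gives an overall error of 0.0496 for four looks (three interim plus final). The 0.018 therefore reproduces as the four-look Pocock value. It holds the error rate only if events are ascertained equally in both arms.

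**3. Phase 2, which also gated review on permanent discontinuation (section 2.19).**
- 7/420 = 1.67% and 17/427 = 3.98%; difference -2.3 points.
- Pooled p = 24/847 = 0.0283. z = 0.0231 / sqrt[0.0283 × 0.9717 × (1/420 + 1/427)] = 2.03, p = 0.042. This matches the stated .04.
- One more 4RIF event (8 vs 17): p = 0.074.
- Hepatitis, 3 vs 16: p = 0.003, as stated. With 4, 5, 6 and 7 events on 4RIF, p is 0.007, 0.017, 0.034 and 0.063. Four more events would be needed to pass 0.05, so this result is sturdier.

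The Phase 2 counts are events attributed to study therapy. An unreviewed event would change them only if it were also attributed.

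**4. Sensitivity in Phase 3 (assumed inputs).** Referral probabilities are not in the protocol. Let both arms have true rate p, and let one arm's events be referred at r times the other's rate. With q1 = rp, q2 = p and n = 3283 per arm (section 2.11):

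s = (q2 - q1) / sqrt{[q1(1 - q1) + q2(1 - q2)] / n}; false-positive rate = 1 - Φ(1.96 - s) + Φ(-1.96 - s).

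For p = 0.04 and r = 0.9: s = 0.004 / sqrt[(0.0347 + 0.0384)/3283] = 0.004/0.00472 = 0.85, giving 0.14.

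The four-look column simulates binomial counts and a pooled z test at 25%, 50%, 75% and 100% of subjects.

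| r | p = 4%: final 0.05 test | p = 4%: four looks at 0.018 | p = 2%: final 0.05 test | p = 2%: four looks at 0.018 |
|---|---|---|---|---|
| 1.00 | 0.05 | 0.05 | 0.05 | 0.05 |
| 0.95 | 0.07 | 0.06 | 0.06 | 0.05 |
| 0.90 | 0.14 | 0.11 | 0.09 | 0.08 |
| 0.80 | 0.41 | 0.33 | 0.23 | 0.18 |
| 0.70 | 0.77 | 0.68 | 0.47 | 0.38 |

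The 3283 per arm includes the Phase 2 subjects. With new participants only (5720/2 = 2860 per arm), the p = 4% final-test values at r = 0.9 and 0.8 become 0.12 and 0.37.

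**5. Effect on the safety looks (assumed inputs).** Suppose 4RIF were truly worse, 6% vs 4%. The chance of crossing 0.018 towards 4RIF harm at the three interim looks is 0.83 with full referral. It is 0.53, 0.21 and 0.04 if 4RIF events are referred at 0.9, 0.8 and 0.7 of the 9INH rate. Under-referral of 9INH events would act the other way and bring spurious signals against 4RIF.

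**The case against.** **A narrow term rather than a contradiction.** Sections 1.6 and 2.4.2 speak of possible SAE, and section 2.9.3 defines possible SAE. On that reading the documents agree. This does not rescue objective (iii) or section 2.18.3, which describe the outcome by grade alone. The narrow term would still make an unblinded decision part of case-finding.

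**The gap may be small.** The site-report trigger is wider than the panel definition, section 2.7.4.4 has all SAE reported on web forms, and sections 2.10 and 2.18.5 record health services used during treatment. RCT Appendix 2 may tie discontinuation to grade, in which case most Grade 3-4 hepatotoxicity would reach the panel. This stands as a limit on size. A reader might infer that such events can never be counted; the documents support only that they have no stated route to review.

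**Direction.** A reader might infer that the rule favours 4RIF, because Phase 2 reported: "Asymptomatic reduction in platelet count and white blood count were significantly more frequent during treatment with 4RIF". The document does not support that. Those reductions are given without a grade and may lie outside the outcome. Nothing shows that physicians stop isoniazid sooner. Section 1.6 urges caution with 4RIF, which could make physicians quicker to stop it.

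**Phase 2.** A reader might also infer that the Phase 2 safety finding is undone. The overall result is fragile, but the hepatitis result is much less so, and Phase 2 fragility is not a Phase 3 effect size.

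**Status and scope.** Section 2.18.3 labels SAE analyses exploratory, and the protocol discloses provider bias. Both count towards severity, yet the same outcome feeds a formal stopping rule. Events after treatment has ended are outside objective (iii) and form no part of this point.

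**Conclusion.** The point holds as an ascertainment weakness in a secondary safety outcome. Followed literally, section 2.9.3 lets an unblinded decision choose which Grade 3-4 events count. Neither blinded grading nor mandatory reporting of provider-stopped therapy repairs that.

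No figure in the protocol is wrong on this point. The bias is possible, not demonstrated; its direction and size cannot be derived from the document, and RCT Appendix 2 could narrow the gap. The sensitivity figures rest on assumed event rates and referral ratios. They show that a relative shortfall of 10% to 20% in one arm's referrals would be enough to matter at this sample size, while one of 5% would matter little. The primary outcome is unaffected. The change should be made, but the trial does not stand or fall on it.

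**What to change.** Align section 2.9.3 with objective (iii) and sections 1.6, 2.4.2 and 2.18.3:

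- Refer every Grade 3-4 clinical or laboratory event detected during treatment to the existing blinded panel, whatever happened to study drug, and make this the trigger for the site report.
- Use these panel-confirmed events for the secondary outcome and for the DSMB looks in section 2.17.2.
- Report events leading to permanent discontinuation as a separate outcome, which keeps a comparison with Phase 2.
- State as a limitation that CBC and transaminases are scheduled only before treatment and at the first follow-up visit. Later laboratory events would still depend on tests ordered by an unblinded provider.

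The cost is protocol and form wording, more dossiers for the panel, and a main SAE count no longer identical to the Phase 2 definition. No added visits or tests are required. Nothing here proposes a rule on when study drug should be stopped.
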